# Methods

## Participants, interventions, and outcomes

### Study setting

This study will be conducted in two high schools: Mianyang Dongchen International School (MDIS) and Mianyang Nanshan High School (MNHS) in Mianyang City, Sichuan Province in China. MDIS is a private school and MHS is a public school.

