### Outcomes

*Primary Outcome Measure*

The success of the intervention is defined as statistically significant more reduction in mean score of PSS-10 in the intervention group as compared with the control group at 12 weeks. The primary outcome measure will be Perceived Stress Scale-10 Items (PSS-10). The PSS-10 is a ten item self-reported scale to assess respondents’ global level of perceived stress (36). Respondents were required to rate the frequency of certain feelings they experienced over the past month on a 5-point Likert Scale (1=never, 2=rarely, 3=sometimes, 4=often, 5=always). It has shown to predict the range of health-related outcomes presumed to be associated with appraised stress (36). The PSS-10 has been translated in Chinese and shown acceptable reliability and validity in both adults (37, 38) and adolescents (39).

*Secondary Outcome Measures*

For secondary outcome meansures, the success of the intervention is defined as statistically significant more reduction in mean score of DASS-21 and statistically significant more increase in mean score of ORS and CISS-SFC in the intervention group as compared with the control group at 12 weeks. Negative mental health outcome will be measured using Depression, Anxiety and Stress Scale (DASS-21). DASS-21 consists of 21 items. Each item is rated on a 4 Likert scale ranging from 0 to 3, indicating to what degree each statement applied to participants over the past week. Summed scores range from 0-42 with more severe symptoms indicated by higher scores. This study will utilize total scores in addition to subscale scores. DASS-21 has been validated in Chinese adolescents and proved to have satisfactory psychometric properties in Chinese adolescent population (40).

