## Assignment of interventions

### Allocation

A two-arm randomized controlled trial will be conducted. Confirmed participants will be randomly allocated in a 1:1 ratio into one of the study groups. Students will be randomised within schools. In order to minimise contamination, students will be randomised on a class basis. Also, students will be notified that all of the participantas will have access to the online program, therefore they should not talk to each other about the content of the intervention. In the intervention group, the participants will use an online stress-managing program which will be delivered via smartphone. Participants in the control group will not use the online program duration. However, they will be notified that they will have access to the online program after 16 weeks (i.e., at the end of the study). The condition to which each participant will be allocated will not be blinded for either experimenters or participants.

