## Methods: Data collection, management and analysis

### Data collection methods

Data relating to perceived stress, negative mental health outcome, positive mental health outcome and coping behaviours will be collected at baseline (T0=0 weeks), post-intervention (T1=12 weeks) and follow-up (T2=16 weeks). Demographic data will only be collected at baseline (see Table1 for study variables). All data will be collected online via the mobile intervention app.

Baseline variables, including demographics, will be gather at the start of the study (Table 1).

Table 2 Study variables

| **Variable** | **Measure** |
| --- | --- |
| Demographic | Age |
|  | Gender |
|  | Grade |
|  | Home location (rural or urban) |
|  | Guardian (parents or others) |
| Perceived stress | PSS-10 |
| Negative mental health | DASS-21 |
| Positive mental health | ORS-4 |
| Coping Behaviors | CISS-SFC |

A description of study instruments along with their reliability and validity are provided below:

The Perceived Stress Scale-10 Items (PSS-10) is a ten item self-reported scale to assess respondents’ global level of perceived stress (36). Respondents were required to rate the frequency of certain feelings they experienced over the past month on a 5-point Likert Scale (1=never, 2=rarely, 3=sometimes, 4=often, 5=always). It has shown to predict the range of health-related outcomes presumed to be associated with appraised stress (36). PSS-10 is a shorter version of Perceived Stress Scale 14-item (PSS-14) that assesses how respondents perceives their lives to be unpredictable, uncontrollable and overloaded (48). The PSS-10 has been validated in populations in different countries and proven to possesses adequate internal consistency with Cronbach’s alpha coefficients ranging from 0.67 to 0.91 (49-54), moderate convergent validity with stressful life events (55), and good concurrent validity with mental health problems such as anxiety and depression (56-58). Particularly, the PSS-10 has been translated in Chinese and shown acceptable reliability and validity in both adults (37, 38) and adolescents (39).

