### Statistical methods

Statistical analyses will be performed using SPSS 22.0 (SPSS Inc., Chicago, IL). We will present descriptive data in a table: categorical variables (e.g., gender, grade, home location etc.) will be presented as counts and percentages. Continuous variables (e.g., age, PSS-10, DASS-21, ORS-4 etc.) will be presented as mean and standard deviation (SD).

To determine whether any significant differences exist between intervention group and control group at baseline, independent t test will be conducted on continuous baseline variables (e.g., age, PSS-10, DASS-21, ORS-4, CISS-SFC, MER), and chi-square analyses will be conducted on categorical or nominal variables (e.g., gender, home location, guardian etc.).

To determine whether the intervention is effective, intention-to-treat (ITT) analyses will be conducted separately (59). The ITT analysis will include the data from the whole randomized sample. A linear mixed model (LMM) will be used to investigate the effects of time and groups on the primary outcome variables. The LMM will be performed with group, time, and group × time as fixed effects. Subjects and schools will be selected as random effects in order to take into consideration both within-subject and within-school correlations. Cohen d effect sizes will be calculated to examine the magnitude of between-group differences. Similar analyses will be conducted for exploring effects on secondary outcome measures.

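### School, a two-level randomisation stratum, is modelled as a random effect, so a school difference in 12-week stress change stays unadjusted in the primary contrast

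*Protocol*

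**What the plan says.** Study setting states: "This study will be conducted in two high schools", one private and one public. Allocation states: "Students will be randomised within schools" and, to limit contamination, "students will be randomised on a class basis". School is therefore the stratum and class the unit of randomisation.

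Outcomes defines success as "statistically significant more reduction in mean score of PSS-10 in the intervention group as compared with the control group at 12 weeks". In the planned mixed model this is the 12-week group × time contrast.

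Statistical methods fixes the model: "The LMM will be performed with group, time, and group × time as fixed effects". It adds: "Subjects and schools will be selected as random effects", to allow for correlation within students and within schools. No fixed school or school × time term is named. Whether the school effect is an intercept or a slope is not stated.

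Assessments are at 0, 12 and 16 weeks. Sample size allows for 10% dropout, and Statistical methods adds: "The ITT analysis will include the data from the whole randomized sample".

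**The concern.** A stratum used in randomisation normally appears in the analysis, and one with two levels belongs in the fixed part. The two schools are the named study sites, not a sample from which a between-school variance can usefully be learned.

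The primary contrast is also a contrast of changes. A school effect that is constant over time has almost no bearing on it. The two schools could still differ in how stress moves over the 12 weeks, for example through different examination calendars. Whole classes are allocated and only volunteers who feel stressed enrol, so the numbers per class will probably vary. Randomising within schools then does not guarantee equal shares of each school in the two arms. Any school difference in change is mixed into the treatment effect to the extent that these shares differ, although the text says that within-school correlation is taken into account.

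**Working it through.** **1. The plan's own scale.** Inputs from Sample size: d = 0.43, SD 5.6, alpha 0.05 (two-sided reproduces it), power 0.80, dropout 10%. The t-test calculation gives 85.87, so 86 per arm and 172 in total; 86/0.90 = 95.6, so 96 per arm and 192 in total. Both figures reproduce. The planned effect in points is 0.43 × 5.6 = 2.41, used below only as a yardstick.

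**2. A variance on 1 degree of freedom.** The 95% interval multiplies the estimate by 1/χ²(1; 0.975) = 1/5.024 = 0.199 and 1/χ²(1; 0.025) = 1/0.000982 ≈ 1,018.

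**3. Why a school intercept drops out.** Write a score as fixed effects + school intercept + student intercept + residual. In the change from baseline to 12 weeks both intercepts subtract away. With complete data the group × time estimate is the difference in mean change, and its variance is 2σ²(1/n₁ + 1/n₂), where σ² is the residual variance. In a simulated balanced trial (150 per arm, fitted σ² = 16.766) this gives √(4 × 16.766/150) = 0.6686, which matches the fitted SE of 0.668649. The school variance does not appear.

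**4. Fits with complete data**, estimate (SE) of 12-week group × time. Rows A and B assume a student SD of 4, a residual SD of 4, and school means 3 points either side of the overall mean.

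| Simulated trial | No school term | Random school intercept | Fixed school only | Fixed school and school × time |
|---|---|---|---|---|
| A: no true school difference in change | 1.2027 (0.6625) | 1.2027 (0.6625) | 1.2027 (0.6625) | 0.8349 (0.6762) |
| B: 4-point school difference in change | 0.0905 (0.6793) | 0.0905 (0.6793) | 0.0905 (0.6793) | −0.5807 (0.6629) |
| C: 2-point difference, 10 unequal classes per school | −1.8624 (0.6548) | −1.8624 (0.6548) | not fitted | −1.4219 (0.6632) |
| D: further check | −1.478 (0.696) | −1.478 (0.696) | −1.478 (0.696) | −1.840 (0.707) |

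Only school × time changes the result. In A the movement is sampling noise, since no school difference in change was simulated. The estimates depend on the assumed values; the equality of the first three columns does not.

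**5. Fits with dropout that differs by school.** At about 10% dropout the estimate is 0.2977 without school, 0.2443 with a random intercept and 0.2436 with a fixed main effect. The movement is 0.053, or 0.053/0.657 = 0.08 of a standard error. At about 25% the values are −0.3558, −0.2750 and −0.2745.

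**6. Size of the unadjusted part.** Shift = (share of intervention students in school B − share of control students in school B) × school difference in change. Assumed, not in the protocol: about 150 volunteers per school, 6 to 20 unequal classes per school, and a 2-point difference.

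| Classes per school | SD of shift | % of 2.41 | 90th percentile of absolute shift | % of 2.41 |
|---|---|---|---|---|
| 6 | 0.41 | 17% | 0.67 | 28% |
| 10 | 0.32 | 13% | 0.52 | 22% |
| 20 | 0.23 | 10% | 0.38 | 16% |

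With only moderately unequal classes the SD is 0.19 to 0.31, so 0.19/2.41 = 8% at the low end. The shift is linear in the school difference: an SD of about 0.10 to 0.21 points at 1 point, and 0.29 to 0.62 at 3 points.

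**The case against.** A reader might infer that the school term cancels exactly and that the primary test is not adjusted for school at all. The documents do not support that. Exact cancellation needs complete data and intercept-only effects, whereas the protocol expects 10% dropout and does not specify the form of the random effect. Level differences between schools are already removed by the within-student contrast. Under dropout the random intercept does adjust: with about 25% dropout, adding 10 points to every score in one school moved the estimate by 0.036 without a school term and by 0.003 with it.

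It is equally tempting to blame the choice of random over fixed. A fixed school main effect gives the same complete-data result, so that choice is not the cause; the absent school × time term is. If the school term barely touches the primary contrast, its poorly estimated variance does little harm there. That variance is very imprecise, not impossible to estimate.

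The shift is a chance imbalance with mean zero, not a systematic bias. Its size rests on assumed figures, and 2 points is 83% of the planned effect. Its SD of 0.2 to 0.4 is below the standard error of about 0.65.

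All of this stands and limits the point. Random-effect details may be left to an analysis plan, but the lists of fixed and random terms are stated here and can be judged. A random school slope would meet the same 1-degree-of-freedom problem.

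**Conclusion.** The point holds in a limited form. The stated model gives a two-level stratum a random effect that does almost nothing for the primary contrast, and it leaves a school difference in 12-week change unadjusted. Under the assumptions in step 6 the resulting shift has an SD of about 8 to 17% of the planned effect. It is zero on average, but in the single allocation drawn it could exceed a quarter of that effect (90th percentile, 6 classes per school). If the schools change alike, or the arms are balanced across schools, there is no systematic shift. This is worth correcting before analysis because the correction is simple, but it does not by itself undermine the trial. Omitting class, the unit of randomisation, from the random effects is the more serious gap in the same sentence.

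**What to change.** In Statistical methods, remove school from the random effects and list the fixed effects as group, time, group × time, school and school × time. If the 12-week score is instead analysed with baseline as a covariate, enter school as a fixed covariate. A fixed school main effect alone in the repeated-measures model is not enough.

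This does not replace accounting for class. A time-constant class intercept would drop out of the change in the same way, so the class term must act on the change or on the baseline-adjusted 12-week score.

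Cost: one sentence, and one degree of freedom (covariate form) to three (school plus two school × time terms). The SE rises when arms are unbalanced across schools: 0.6762/0.6625 = 1.02 in A, 0.6632/0.6548 = 1.01 in C and 0.707/0.696 = 1.02 in D, so about 1 to 3% is typical. Stronger imbalance costs more: in the 10% dropout example the ratio was 0.6877/0.6557 = 1.05. Where the schools really differ in change the SE can fall, as in B (0.6629/0.6793 = 0.98).

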## Monitoring

### Data monitoring

There will not be interim analyses, analyses will only be done at 16 weeks after the randomization.

### Harms

In our study an adverse event will be defined as serious psychological distress experienced by participants without regard to the possibility of a causal relationship. Adverse events will be collected after the subject has provided consent and enrolled in the study. If a subject experiences an adverse event after the informed consent document is signed but the subject has not started to receive study intervention, the event will be reported as not related to study intervention. All adverse events occurring after entry into the study will be recorded. If an adverse event meets the criteria for a serious adverse event after study enrolment, this will be reported to Centre for Online Health, The University of Queensland. If the participant drop out as a result of an adverse event, study personnel will document the circumstances and data leading to discontinuation of the intervention. A serious adverse event for this study is any occurrence that is believed by the investigators to be causally related to the intervention and results in any of the following: Life-threatening condition (i.e., suicidal ideation or attempts), hospitalization due to mental health conditions, drop out of school.

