### Interventions

The intervention group will download a stress-managing app, the app can be used on mobile devices including mobile phones and tablets etc. The app will be based on Stress Inoculation Training (SIT) developed by Meichenbaum (29). Even though SIT was designed for military settings, there has been a lot of studies which adapted the SIT and use it among students and adolescents (30-34) and delivered SIT via technologies (35). Our study will modify SIT to high school context by adding assertiveness and training participants cognitive and behavioural techniques to deal with stressors arising from academic environment and peer interpersonal relationships. The online stress-managing intervention will comprise of 11 sessions which consist of psychoeducation, problem assessments, training of stress coping skills (emotion-focused coping skills and problem-focused coping skills), cognitive restructuring, imagery and behavioural rehearsal and role play (see [Appendix 1](#_Appendix_1) for details of the intervention content). The intervention content will be in Chinese language. The control group will not be given access to the app until the termination of the trial (12 weeks after the start of the trial). There will be no other intervention given to the control group. Both the intervention group and the control group will have full access to usual care, which is the psychological courses arranged by the high schools.

The criteria for discontinuing for a given trial participant include: (i) if they self-reported or reported by others to be suicidal; (ii) if they drop out of school during the intervention period; (iii) if they require to withdraw from the study.

Strategies to improve adherence to intervention protocol include:

- Instructions about the importance of following study guidelines for adherence to once weekly product.
- Instructions about the purpose and use of the intervention app.
- Notification sent via app weekly on each Sunday that there will be a session taken in the app.
- Successfully completion of each session will generate a virtual star in the participant’s account as a reward for the participation.
- Adherence assessments include log in times and other usage data collected in the app.

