### Participant timeline

Table 1 and Figure 2 illustrate the time schedule of enrolment, randomization, interventions, and assessments for participants.

Table 1 Perceived Stress Reduction Protocol Schedule of Forms and Procedures

|  | | | **-1** | **T0** | **T1** | **T2** |
| --- | --- | --- | --- | --- | --- | --- |
| **Activity/**  **Assessment** | **Staff**  **Member** | **Approximate**  **Time to**  **Complete** | **Pre-Study**  **Screening/ Consent** | **Pre-Study**  **Baseline/**  **Randomization** | **Post-study**  **12 weeks** | **Follow-Up**  **16 weeks** |
| Consent Form | Head teachers | 20 Minutes | X |  |  |  |
| Inclusion/  Exclusion Form | Principal investigator | 5 minutes | X |  |  |  |
| Demographics Questionnaire | Principal investigator | 10 Minutes |  | X | X | X |
| PSS-10 | Principal investigator | 10 minutes |  | X | X | X |
| DASS-21 | Principal investigator | 20 minutes |  | X | X | X |
| ORS-4 | Principal investigator | 5 minutes |  | X | X | X |
| CISS-SFC | Principal investigator | 20 minutes |  | X | X | X |
| Randomization | Principal investigator | 15 Minutes |  | X |  |  |

[figure not shown]

Figure 2 Participant Timeline

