Negative mental health outcome (i.e., anxiety, depression and stress) will be measured using Depression, Anxiety and Stress Scale (DASS-21). DASS-21 consists of 21 items. Each item is rated on a 4 Likert scale ranging from 0 to 3, indicating to what degree each statement applied to participants over the past week. Summed scores range from 0-42 with more severe symptoms indicated by higher scores. This study will utilize total scores in addition to subscale scores. DASS-21 has been validated in Chinese adolescents and proved to have satisfactory psychometric properties in Chinese adolescent population (40).

Positive mental health status will be measured using Outcome rating scale (ORS). The ORS is a four-item self-report instrument. The ORS was developed as a brief alternative to the Outcome Questionnaire-45 (OQ-45)-a widely used and well-validated measure (41). The ORS was designed to assess change in three areas of client functioning generally considered valid indicators of treatment progress: individual (or symptomatic) functioning, interpersonal relationships, and social role performance (work adjustment, quality of life). The ORS was found to have adequate reliability and validity (42). The Chinese version of the ORS was recently validated in Chinese sample and showed to be a reliable and valid measure for Chinese sample and sub-clinical clients (43).

Stress coping behaviours will be measured using the short form of Coping Inventory for Stressful Situations (CISS-SFC). The CISS-SFC is a 21-item scale which measures three dimensions of coping-task-oriented coping, emotion-oriented coping, and avoidance-oriented coping. CISS-SFC has been translated into Chinese and approved to be satisfactorily valid and reliable among Chinese university students (44).

The usability and acceptance of the program will be assessed in order to gain information about users’ needs and specificities to improve interfaces of online programs for Chinese adolescents. Acceptance of the online program will be assessed by providing the users’ opportunity to write feedback at the end of each sessions. The contents of the written feedback of the online program will be evaluated. Usability will be assessed using measures such as the time they spent with the program and by the number of sessions they completed.

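### No method or schedule common to both arms is stated for finding adverse events, and the DASS-21 has no stated safety use

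*Protocol*

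**What the plan says.** The Harms section gives the definition: "an adverse event will be defined as serious psychological distress experienced by participants without regard to the possibility of a causal relationship". It adds a promise of complete capture: "All adverse events occurring after entry into the study will be recorded". It does not say by what question, at which visit or by whom events are to be found. A serious adverse event is defined more narrowly, as "any occurrence that is believed by the investigators to be causally related to the intervention" with one of the listed consequences.

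Suicidality appears in the Interventions section as a reason for discontinuing a participant: "if they self-reported or reported by others to be suicidal". No other route for detecting it is given.

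The schedule ("Table 1 Perceived Stress Reduction Protocol Schedule of Forms and Procedures") lists consent, eligibility, demographics, the four questionnaires and randomisation. It contains no form or procedure for harms.

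The Interventions section has the app arm prompted to a session every week and keeps the control arm off the app during the trial. On session feedback, Data collection methods says: "Acceptance of the online program will be assessed by providing the users’ opportunity to write feedback at the end of each sessions".

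The DASS-21 is completed by both arms at weeks 0, 12 and 16. The Outcomes and Statistical methods sections use it for group description, baseline comparison and secondary efficacy. No cut-off, alert or review of an individual score is mentioned. The Blinding section says that neither participants nor researchers are blinded after assignment.

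**The concern.** A promise to record all events is only as good as the means of finding them, and here the means are left open. Run on the stated schedule, the study would ask no student in either arm about harm. What is recorded would depend on what happens to come to someone's notice, and that opportunity differs by arm: one arm writes to the study after each weekly session, while the other has no scheduled contact until week 12. With everyone aware of allocation, a difference in adverse-event counts could then arise from the amount of contact and not from the app.

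The population makes this more than a formality. Recruitment targets students who consider themselves stressed, and the Background section says that stressed adolescents are at higher risk of suicide. Eligibility excludes diagnosed or treated mental illness, so an undiagnosed but severely distressed student can enter. That student completes a DASS-21 at baseline, yet the protocol states no step by which the score would be looked at for safety.

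**Working it through.** The plan gives no figure on this point, so there is nothing to reproduce. The check sets the sections side by side.

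**1. Is there a stated method of finding events?**
- Harms: definition and promise to record; no instrument, question, threshold, visit or responsible person.
- Table 1: no harms row.
- Interventions: suicidality known through the participant or others.

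The method is unstated. It is not stated to be passive, but nothing active is scheduled.

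**2. Is contact equal between arms?**
- App arm: weekly sessions, each with free-text feedback, plus questionnaires at weeks 0, 12 and 16.
- Control arm: questionnaires at weeks 0, 12 and 16, with nothing scheduled by the study between weeks 0 and 12.
- Both arms: school, the schools' psychological courses, and possible report by teachers or others.

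Scheduled study contact is unequal; informal routes exist in both arms.

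**3. Can the size of the resulting bias be derived?** Let n = 150 per arm (Sample size section), p the true rate of serious distress, equal in both arms, and a and c the probabilities that an event is captured in the app and control arms. Expected recorded events are n × p × a and n × p × c, so their ratio is a / c whatever the values of n and p. The documents give none of p, a or c. All values below are assumptions:

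| p | a, c | App arm | Control arm | Ratio |
|---|---|---|---|---|
| 2% | 0.8, 0.4 | 150 × 0.02 × 0.8 = 2.4 | 150 × 0.02 × 0.4 = 1.2 | 2 |
| 5% | 0.8, 0.4 | 6.0 | 3.0 | 2 |
| 10% | 0.8, 0.4 | 12.0 | 6.0 | 2 |
| 5% | 0.9, 0.9 | 6.75 | 6.75 | 1 |

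The ratio only returns the assumption. The table shows the mechanism; it does not estimate the bias.

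**4. What could the DASS-21 add?** It is collected on the same schedule in both arms, so it is not subject to the contact imbalance. Its recall period is the past week. After baseline it therefore covers one week before T1 and one before T2, that is 2 of 16 weeks (2/16 = 12.5%). The documents do not say that it covers suicidality. It can supplement a solicited harms question but cannot replace one.

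**5. Serious events.** Because the definition requires belief in a causal link to the intervention, a control student without the app can hardly have a serious adverse event. This is a separate weakness of the between-arm comparison, which better detection would not cure.

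**The case against.** The best defence is that the protocol does commit to collecting and recording all adverse events, that teachers and others can report on students in both arms, and that the principal investigator is on site during the intervention period. That is fair: controls do not lack every route. A reader might set 11 or 12 weekly reporting opportunities against none, but the text does not support that count. Session feedback is collected to judge acceptance; it is not called a harms channel, and nothing says it is read for distress during the trial. It is only a place where distress could surface.

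Three further inferences are tempting and should be resisted.
- That the app arm would show a threefold excess of events: this follows only if one assumes capture of 60% against 20%, and neither figure is in the documents.
- That a distressed student would go unnoticed for 16 weeks: the statement that "analyses will only be done at 16 weeks after the randomization" concerns analyses, not sight of individual questionnaires, and Table 1 names the principal investigator for the DASS-21. No review of scores is stated, but neither is that delay.
- That the trial could not tell whether the app increases distress: DASS-21 total and subscale scores are compared between groups over time, so a mean worsening could show there.

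It could also be said that such detail belongs elsewhere. How and when harms are solicited is trial conduct, which the Harms section and the schedule are there to settle; it is not a matter normally left to a statistical analysis plan. The consent materials and the section on trial oversight were not available for this check, so the finding is limited to the protocol text that was.

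**Conclusion.** The point stands in limited form. The protocol states no method or schedule, identical in both arms, for finding the events it defines; contact scheduled by the study is heavier in the app arm; and the DASS-21, which both arms complete three times, has no stated safety use. Adverse-event counts by arm may therefore reflect opportunity to report. The size of this effect is unknown, and its presence rests on the assumption that extra contact in the app arm brings some events to light that would be missed among controls.

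The efficacy analysis is not affected, and the comparison of mean DASS-21 scores remains a valid look at average distress. What that comparison cannot do is identify individual students or stand in for counts of serious distress: a few marked deteriorations can leave a mean almost unchanged. The change should be made before enrolment, because events that were never asked about cannot reliably be recovered afterwards.

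**What to change.** 1. Add one solicited harms question, identical in wording and mode in both arms, to the T0, T1 and T2 questionnaires, and a harms row to Table 1. At T1 and T2 it should cover the time since the previous questionnaire. The statement that all data come through the intervention app must be reconciled with the control arm's lack of access, so that both arms can answer in the same way.
2. Base the between-arm comparison on solicited events. Report events that surface only through app feedback separately.
3. Score the DASS-21 on submission at each time point. Bring scores meeting a threshold that the team fixes in advance to the principal investigator's attention, and tabulate them by arm as a safety summary alongside the harms question.

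The direct cost is one question, one row in the schedule and automated scoring of data already collected. There are two downsides. More events will be recorded. And because the Interventions section counts students referred for mental health assistance as drop-outs, flagging may add attrition, possibly among the most distressed. The provisions on discontinuation and referral (Interventions), adverse events (Harms) and counselling (Ancillary and post-trial care) must be reconciled by the team before flagging starts; no clinical rule is proposed here.
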